## Abstract

**Background:**

Diabetes is a major challenge for the health care system and especially for the primary care provider. The Chronic Care Model represents an evidence-based framework for the care for chronically ill. An increasing number of studies showed that implementing elements of the Chronic Care Model improves patient relevant outcomes and process parameters. However, most of these findings have been performed in settings different from the Swiss health care system which is dominated by single handed practices.

**Methods/Design:**

CARAT is a cluster randomized controlled trial with general practitioners as the unit of randomization (trial registration: ISRCTN05947538). The study challenges the hypothesis that implementing several elements of the Chronic Care Model via a specially trained practice nurse improves the HbA1c level of diabetes type II patients significantly after one year (primary outcome). Furthermore, we assume that the intervention increases the proportion of patients who achieve the recommended targets regarding blood pressure (<130/80), HbA1c (=<6.5%) and low-density lipoprotein-cholesterol (<2.6 mmol/l), increases patients' quality of life (SF-36) and several evidence-based quality indicators for diabetes care. These improvements in care will be experienced by the patients (PACIC-5A) as well as by the practice team (ACIC). According to the power calculation, 28 general practitioners will be randomized either to the intervention group or to the control group. Each general practitioner will include 12 patients suffering from diabetes type II. In the intervention group the general practitioner as well as the practice nurse will be trained to perform care for diabetes patients according to the Chronic Care Model in teamwork. In the control group no intervention will be applied at all and patients will be treated as usual. Measurements (pre-data-collection) will take place in months II-IV, starting in February 2010. Follow-up data will be collected after 1 year.

**Discussion:**

This study challenges the hypothesis that the Chronic Care Model can be easily implemented by a practice nurse focused approach. If our results will confirm this hypothesis the suggestion arises whether this approach should be implemented in other chronic diseases and multimorbid patients and how to redesign care in Switzerland.

## Background

Chronic diseases and multimorbidity are the major challenge for the future health care system [1]. Since chronic diseases not only impact individuals' quality of life but also represent a tremendous economical burden, many approaches have been made to increase patients' quality of life and to reveal affordable disease management tools. Based on the evidence of these interventions, summarized in a review of Tsai et al., Wagner and colleagues developed the Chronic Care Model (CCM) as a conceptual framework [2-5]. The aim of the CCM is to integrate all evidence-based concepts or approaches into this conceptual framework. One of the major problems addressed by the CCM is the fact that current care of chronically ills is often reactive and triggered by actual problems instead of being proactive, structured and planned [6]. Based on the current evidence, the CCM contains 6 key dimensions of care: Organization of health care, clinical information systems, delivery system design, decision support, self-management support, and community resources.

Most of the data supporting the concept of the CCM has been collected in settings in the U.S., primarily HMOs, which do not exist in most European countries. In Switzerland, the majority of the practices are single handed and privately owned. The system is very physician-centered; practice nurses are only marginally involved in the diagnostic and therapeutic process. One reason might be that the proportion between physicians and inhabitants is very high in Switzerland compared to other developed countries. As many other countries, Switzerland is faced with huge demographic changes, leading to a rising number of older and chronically ill inhabitants. On the other hand, the number of GPs is decreasing over many years. Consequently, new, more team-oriented approaches in the care for chronically ills are indispensable. Nevertheless, GPs in small, single handed practices are momentarily the main provider of care for chronically ills including diabetics in the Swiss health care system. Large specialist care centers do not exist; endocrinologists are only used for consultations in difficult treatment situations. Interestingly, electronic patient records, an important tool in the treatment and especially follow-up of chronically ills are not well established in Switzerland. As recent data showed, only about 10% of GPs work with electronic patient records (Zoller et al., Swiss Medical Weekly, submitted). Therefore, it is unclear if and to what extent the results generated in the U.S. settings are transferable to Europe or Switzerland in particular. Due to its widespread acceptance the CCM has achieved, an intense discussion has started among European physicians if and how the CCM or its components can be implemented in health care [7,8].

Regarding diabetes, valid data on the prevalence in Switzerland is not available. In Germany for example the overall prevalence of diabetes for the 25- to 65-year-old population was 5.34% in 2002-2005 [9] and therefore less than in the U.S. where the prevalence was estimated to 20.8 million (7% of the population) [10]. Data form the U.S. show that the expenditures for patients with diabetes are at a rate 2.3 times higher than those without the disease [11].

Several studies have shown that there is considerable potential to improve the process and outcome of diabetes care in general practice. Some studies showed that 28% diabetic patients in general practices have poor glycemic control and 55% have a high body mass index [12]. Structured programs as the disease management programs introduced in Germany have shown to improve the quality of care [13] but results regarding clinical outcomes are not yet available. Unfortunately, such programs involving the practice nurse in the treatment have not been assessed in Switzerland.

Implementing changes in primary care, especially new concepts of care with the complexity as the CCM, represents a big challenge. It is well known that strategies to implement changes in primary care vary widely in their effectiveness to change clinical practice. For instance, passive dissemination of information is generally ineffective for altering health professional behavior [14], while audit with feedback has a small to moderate effect [15]. Multifaceted interventions targeting different barriers to change tend to be more effective than single interventions [16]. Educational outreach visits can also change professionals' behavior [17]. Self management is the primary goal of diabetes education interventions. Diabetes associated complications are preventable in most cases. Research showed that control of glucose (HbA1c), blood pressure (BP) and low-density lipoprotein (LDL) cholesterol seem to be the most important targets to avoid microvascular and macrovascular complications of diabetes [18,19].

Diabetes impacts quality of life tremendously [20,21] and increases the incidence of depression [22], which is an important comorbidity in most chronic diseases. Depression or depressed mood has a negative effect on patients' ability to carry out self-management [23] and can in consequence worsen the glycemic control [23,24]. Prior studies in diabetes indicated that depression is recognized and treated in about 33% of patients, even though psychotherapy and psycho pharmacotherapy have been shown to have significant beneficial effects on mood and glycemic control [25-27].

In daily routine an obvious gap between recommendations and clinical practice can be observed, since the majority of patients (93%) do not achieve the recommended goals for HbA1c, LDL and BP [28-30]. The figures vary depending on the observed setting, but it can be assumed that over one-third of adults have HbA1c levels above recommended thresholds [29]. Other studies indicated that 32% are above a BP of 130/80mmHg, 66.2% have LDL values >2.6 mmol/l and nearly a third of the patients do not receive recommended annual eye (32.3%) or foot (31.7%) exams [31]. Regarding the thresholds in this study, we decided to choose a HbA1c level of 6.5% since the guidelines of the AHA and ADA recommend a level of 7.0% as general target and a level of 6.0% as ideal target [32].

This study challenges the hypothesis that implementing elements of the Chronic Care Model via a specially trained practice nurse in team work with the general practitioner improves the HbA1c level of diabetes type II patients in small, single handed practices in Switzerland significantly after one year (estimated change: 0.5) and increases the proportion of patients who achieve the recommended targets [32] regarding blood pressure (<130/80), HbA1c (=<6.5%) and LDL-cholesterol (<2.6 mmol/l) significantly.

Furthermore, we assume that this implementation improves patients' quality of life (SF-36) and several relevant quality indicators for diabetes care.

Finally we hypothesize that these improvements in care aiming at a better accordance with the CCM will be experienced by the patients as well as by the practice team, reflected in increased scores in the Patient Assessment of Chronic Illness Care (PACIC-5A) and Assessment of Chronic Illness Care (ACIC) instruments.

## Methods/Design

### Outcome-Parameter

The outcome parameters and instruments which are used in the study are summarized in Table 1.

**Table 1 T1:** Outcome-parameters and instruments of the study

Outcome-Parameter (Patient)	Parameter/Instrument
**Primary Outcome**	HbA1c level

**Secondary outcomes**	

**- Guideline adherence (recommended treatment goals)**	% of patients reaching goal HbA1c (< 6.5%), LDL-Cholesterol (< 2.6 mmol/l); blood pressure (< 130/80mmHG)

**- Quality of life**	SF-36

**- Process quality**	

	% patients receiving at least one eye examination per year

	% patients receiving at least one food examination per year

	% patients receiving at least one nephropathy screening per year

	% patients receiving at least one neurological testing

**- Accordance to the CCM**	PACIC 5A (patients perspective)

	ACIC (provider perspective)

**Confounder control**	PHQ-9 (depression)

### Primary outcome

The primary outcome is the glycated haemoglobin (HbA1c) level. The power calculation is based on this parameter.

### Secondary outcomes

#### Guideline adherence (recommended treatment goals)

The proportion of patients who achieve the recommended targets for diabetes patients [32] regarding blood pressure (<130/80), HbA1c (=<6.5) and LDL-cholesterol (<2.6 mmol/l).

#### Quality of Life (QoL)

Even though the HbA1c is the most common parameter in diabetes trials, the quality of life is an important outcome parameter. Furthermore, recent studies have shown that decreasing the HbA1c aggressively can be associated with severe side effects, most likely due to hypoglycemia. In general, disease specific instruments should be favored against generic instruments, especially due to a higher sensitivity to change. Regarding diabetes, several instruments to assess QoL have been developed. Since none of them has so far proven to be superior over the well established SF-36 [33], which has already been used in large diabetes trials in primary care, we decided to use this instrument.

#### Quality indicators

Quality indicators can be based on process measures or clinical outcome measures. To enable international comparisons, we decided to asses quality indicators for diabetes according to the recommendations of the American Diabetes Association [34]. These quality indicators for diabetes care are also used e.g. by the British National Diabetes Quality Improvement Alliance. The indicators reflect the physical examination (incl. feet) and referrals (incl. eye):

P1: Percentage of patients receiving at least one nephropathy screening per year

P2: Percentage of patients receiving a dilated eye examination or evaluation of retinal photography by an ophthalmologist or optometrist per year

P3: Percentage of patients receiving at least one foot examination per year

P4: Percentage of patients receiving at least one peripheral neurological testing per year

#### Accordance to the Chronic Care Model (CCM)

##### Patients' perspective

Patients assessment of the provided care will be assessed with the Patient Assessment of Chronic Illness Care (PACIC 5A) which has been developed to assess congruency of provided health care to the CCM [35]. It is organized according to the key elements of the CCM and assesses the behavior of professionals and practice teams from a patient's perspective. The PACIC 5A contains 20 items assessing 5 scale constructs: patient activation, delivery system design/decision support, goal setting/tailoring, problem solving/contextual, follow-up/coordination. "Patient activation" assesses to what extent the patient was motivated and supported by the physician to initiate changes. "Decision support" assesses if the patient was supported e.g. by booklets and how satisfied he was with the organization of his care. "Tailoring" assesses to what extent general instructions and suggestions were adapted to his personal situation. "Problem solving" addresses how the physician dealt with problems which interfered with achieving predefined goals. Finally, "Follow-up" addresses how frequently and consequently the whole process was followed-up. Recently, a German version of the PACIC 5A has been validated in a sample of osteoarthritis patients [36]. The "5A" model represents an evidence-based approach to induce a behavioral change [37]. Glasgow et al. expanded the PACIC 5A by including 6 items assessing to what extent physicians' counseling reflects the 5A-approach which represents the recommended counseling approach for behavioral changes according to the recommendations of the US Preventive Services Task Force (USPSTF). The PACIC 5A was validated in a sample of diabetes patients [38].

##### Provider perspective

To assess accordance to the CCM of the health care provider's perspective, the Assessment of Chronic Illness Care (ACIC) [39] will be used. The ACIC is aimed at organizational teams to help identifying areas for improvement in their care for chronic illnesses and to evaluate the level and nature of improvements made in their system. It consists of 28 items covering the six areas of the CCM: Organization of the healthcare delivery system (6 items), community linkages (3 items), self-management support (4 items), decision support (4 items), delivery system design (6 items) and clinical information systems (5 items). Responses fall within four descriptive levels (D, C, B, A) of implementation ranging from D "little or none" to A, a "fully implemented" intervention. Within each of the four levels, respondents are asked to choose one of three ratings of the degree to which that description applies. The result is a 0-11 scale, with categories defined as follows: 0-2 (little or no support for chronic illness care), 3-5 (basic or intermediate support for chronic illness care), 6-8 (advanced support) and 9-11 (optimal, or comprehensive, integrated care for chronic illness). Subscale scores for the six areas are derived by summing the response. Bonomi et al. showed all six ACIC subscale scores to be responsive to health care quality-improvement efforts [39]. A translated and culturally adapted version into German (G-ACIC) has just been validated by the authors (submitted).

### Confounder control

Depression has been revealed as a potential confounder on quality of life and on satisfaction with care in most chronic diseases, including diabetes. Depression is also an independent predictor of mortality in many chronic diseases [40,41]. It also influences the assessment of the provided care with the PACIC 5A. Thus, depression will be assessed by means of the Patient Health Questionnaire, short form PHQ-9 [42]. This instrument has been proven to be a valid and reliable tool and has already been used in previous studies in primary care as e.g. the PraxArt trial [43,44].

### Study design

The study is a (prospective) cluster-randomized, open, two-armed intervention study with the GP as the unit of randomization. The design of a cluster randomized study was chosen because this design has optimal internal validity, while avoiding contamination of interventions associated with patient randomization. The flow chart of the study is described in Figure 1.

**Figure 1 F1:**
[figure not shown]
**Flow chart of the study**.

### Sample size

Due to its hierarchical structure, sample size calculations for cluster randomized trials differ from sample size calculations for common RCTs [45,46]. The required number of patients increases with the intracluster correlation, estimated in the intracluster correlation coefficient [47]. Based on our previous studies and on data available at the website of the University of Aberdeen [48], we assumed an ICC of 0.04 for the primary outcome. As primary outcome we defined the HbA1c. The sample size calculation was performed with the Cluster Randomization Sample Size Calculator ver.1.02 of the University of Aberdeen.

Unfortunately, no epidemiological data regarding the HbA1c is available from the Swiss primary care setting. Based on previous data and on our inclusion criteria (HbA1c > 7.0%) we assumed a mean HbA1c of 7.7% at pre-data-measurement time and aimed at a reduction in the HbA1c of 0.5% points with the intervention. In accordance to the data from the "Diabetes in Germany" (DIG)-study [49] and the ACCORD trial [50], the SD was assumed to be 1.2. The power was defined as 80%. The significance level was defined to be 0.05. Based on these assumptions and definitions we have to include 12 patients and 11 practices in each arm. In cluster randomized trials a higher drop out rate has to be assumed since the drop out of one cluster leads to the loss of all patients in a cluster. Therefore we assumed a drop out rate of 20%, resulting in 14 practices in each arm and 28 in total [45,46,51].

### Recruitment of GPs and randomization

The GPs are the unit of randomization. They are eligible for randomization if they participate in the routine primary care of unselected patients to assure that patients of all social levels have unlimited admission to the practice. If they are working in a non-single-handed practice, it is important that they have their own patients which can clearly be allocated to them. From an address database of all GPs in the area of Zurich, St. Gallen and Appenzell every second GP (about 800 GPs in total) was randomly selected, informed about the study and invited to an information meeting by a formal letter of the Department of General Practice and Health Services Research of the University of Zurich at the end of November 2009. Additionally, the project was presented in several quality circle meetings in doctors' networks (regions Zurich, Winterthur, St. Gallen). The aim of the information meeting was to provide the GPs with detailed information on the purpose and the associated effort for participating as well as to give an overview on the course of the whole study. If a GP was not able to attend the meeting but was interested in participation, he was invited to contact the Department of General Practice and Health Services Research and was delivered detailed information about the study by a project assistant.

The GPs who finally agree to participate will be alphabetically ordered in a list with numbers from 1 to 28 (no constraint will be imposed to cluster randomization). With the statistical program SPSS (version 18.0), 14 figures out of 28 will be randomly generated which represent the intervention group. The GPs with the corresponding numbers will be allocated to the randomly generated figures and to the intervention group, respectively. The randomization will be performed by an independent assistant who is not involved in the study and who is blind to the identity of the GPs. GPs will be informed about the group they have been randomized to after the inclusion of patients has been completed to avoid any bias in including patients.

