##### Intervention on the practice nurse

In Switzerland, as in most European countries, the education of practice nurses differs tremendously from the U.S. and it is completely unknown if approaches as in the U.S. can be implemented. The education of practice nurses in Switzerland is less focused on medical issues and addresses mainly administrative matters. Lacking medical knowledge has been identified as an important barrier towards an increased involvement of practice nurse in medical care. Unfortunately, professions as advanced nurse practitioners or physicians' assistants do not or only marginally exist. Therefore, practice nurses represent the only resource for a team approach in primary care. This study challenges the hypothesis that CCM appropriate care can be implemented in primary care. To qualify practice nurses to do so, practice nurses from the intervention group will participate in the well established educational course "Treatment of long term patients - module diabetes" ("Betreuung von Langzeitpatienten - Modul Diabetes"). The course lasts 6 days and will be organized by the union of Swiss practice nurses ("Schweizerischer Verband medizinischer Praxisassistentinnen") [56]. The content of the course is the treatment of diabetes patients (medical basics, diet, practical tips, communication etc.), the role of the practice nurse in a team providing structured care for chronically ills and how to perform a follow-up with the CARAT-monitoring-tool. The tool addresses clinical parameters (e.g. HbA1c, blood pressure, LDL etc.), performed examinations (food control, neurological tests, eye examination etc.) as well as referrals and adherence to the prescribed drugs and other recommendations. The tool contains a traffic-light-scheme, indicating if worsening or improvement has occurred. While giving a quick overlook over the status, the traffic-light-scheme will ease the follow-up for the physician who receives the CARAT-tool after it has been filled out by the practice nurse.

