#### 2. Clinical intervention - Intervention on the patient

The Chronic Care Model has been shown to provide interactions between patients and providers that support optimal patient functional and clinical outcomes [57,58]. Practice nurses were chosen to implement and to deliver the intervention because of the ongoing need for assessment of goal attainment and because of their ability to work with patients to reduce ambivalence to behavior change, collaborate with GPs and reinforce diabetes education. In the European setting, external nurse practitioners do not exist or are not accepted by GPs. In contrast, the practice nurses are already integrated in the primary care setting and have a continuous relationship with study participants including both direct clinical interventions and collaboration with their GP.

The 6 key elements of the CCM will be addressed as follows:

Organization of health care: The specially trained practice nurse will be involved in care. She will monitor the patient during the study with the CARAT-tool. Contacts for monitoring are planned at least every 4 moths but the frequency can be increased according to the clinical situation of the patient. The clinical aim is to assure that standing orders for established clinical practice guidelines regarding frequency of laboratory testing (HbA1c, LDL, nephropathy screening), yearly ophthalmologic exam and performance of foot exam by the nurses facilitates are met.

Clinical information systems: The information on monitoring and appointments with the practice nurse will be collected in the CARAT-monitoring-tool and will be forwarded to the GP based on importance/urgency before the patient encounter to the GP. This way of information transfer between practice nurse and GP is new. This improvement in communication should help the GP to get an immediate overview on the current situation of the patient. It should also help to address current problems - as for instance a detected depression - more accurately. Data entry by the nurses into the registry allows the GP to obtain an overview on self-care goals, clinical parameters over time (BP, HbA1C, LDL, last ophthalmologic exam, aspirin use, foot exam) via a single sheet prior to each patient visit, and provides prompts for issues to be addressed at a given visit.

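### GPs are drawn one by one although the nurse-delivered intervention belongs to the practice, so two GPs sharing a nurse could land in opposite arms; the practice should be the unit.

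*Protocol article*

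**What the plan says.** The article names two different units.

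- **The GP.** Study design and Recruitment of GPs and randomization both name the GP; the latter states "The GPs are the unit of randomization". The participating GPs are listed alphabetically and "14 figures out of 28 will be randomly generated which represent the intervention group", with the remark that "no constraint will be imposed to cluster randomization". The assistant who makes the draw does not know who the GPs are.
- **The practice.** Sample size applies the dropout allowance to practices, "resulting in 14 practices in each arm and 28 in total". Intervention on the GPs also describes the allocation step as one of practices.

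Group-practice GPs may take part, on one condition: "If they are working in a non-single-handed practice, it is important that they have their own patients". That condition settles which GP a patient belongs to. It does not say which nurse looks after the patient.

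The section on the clinical intervention says "Practice nurses were chosen to implement and to deliver the intervention" and, on the organisation of care, "The specially trained practice nurse will be involved in care". Training follows the arm: "practice nurses from the intervention group will participate in the well established educational course".

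Study design justifies the cluster design partly by the avoidance of contamination between treatments.

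**The concern.** Clustering protects against contamination only if whatever carries the intervention lies wholly inside one cluster. Here much of it is carried by the practice nurse and the practice's way of working. A group practice with two enrolled GPs is therefore two clusters on the allocation list but may have one nurse. If the GPs are split, a nurse trained for the intervention arm also sees the control GP's patients. The control arm then receives part of the intervention, and the estimated difference is biased towards zero. This cannot be repaired after allocation.

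Two further consequences follow. First, GPs who share staff and premises are likely to have correlated results, while the sample size formula treats the clusters as independent. Secondly, the ACIC is aimed at teams, so a split practice would supply much the same team to both arms. The process indicators that the nurse is trained to follow up, such as foot and neurological examinations, are open to the same leakage as HbA1c.

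**Working it through.** **Inputs from Sample size:** difference 0.5 HbA1c points, SD 1.2, ICC 0.04, 12 patients per cluster, power 80%, significance level 0.05 (taken as two-sided), dropout 20%.

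**The plan's own figure.**

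1. Patients per arm without clustering: 2 × [1.2 × (1.960 + 0.842) / 0.5]² = 90.4, rounded up to 91.
2. Design effect: 1 + (12 − 1) × 0.04 = 1.44.
3. Clusters per arm: 91 × 1.44 / 12 = 10.92, rounded up to 11.
4. After 20% dropout: 11 / 0.8 = 13.75, rounded up to 14.

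The stated 11 and 14 are reproduced. A one-sided test would give 8.64, hence 9, so the two-sided reading is the right one. The arithmetic is sound; it assumes independent clusters and no contamination.

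**Chance that colleagues are split.** Once one GP of a pair is placed, 14 of the remaining 27 places are in the other arm, so the probability is 14/27 = 51.9%. With two such pairs among the 28, the chance that neither is split is [C(24,14) + 2 × C(24,12) + C(24,10)] / C(28,14) = 23.3%. The chance of at least one split is therefore 76.7%.

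**Dilution.** The article does not give the number of control GPs affected, *q*, or the share of the effect that reaches their patients, *c*. Both are assumptions here.

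- Diluted difference = 0.5 × (1 − *c* × *q* / 14).
- Effective patients per arm with *k* clusters: 12*k* / 1.44, which is 91.7 for 11 clusters and 116.7 for 14.
- Standard error: 1.2 × √(2 / effective patients), which is 0.177 for 11 clusters and 0.157 for 14.
- Power = Φ(difference / SE − 1.96), a normal approximation.

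| Control GPs affected | Carry-over | Difference | Power, 11 per arm | Power, 14 per arm |
|---|---|---|---|---|
| 0 | – | 0.500 | 80.5% | 88.9% |
| 1 | 50% | 0.482 | 77.6% | 86.6% |
| 1 | 100% | 0.464 | 74.5% | 84.0% |
| 2 | 50% | 0.464 | 74.5% | 84.0% |
| 2 | 100% | 0.429 | 67.6% | 77.9% |

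Eleven per arm means that the whole dropout allowance is used up; 14 means that no cluster is lost.

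**Non-independence.** With probability 13/27 = 48.1% the two colleagues land in the same arm. There is then no contamination, but two correlated clusters are counted as two independent ones. The article gives no between-practice correlation, so no figure can be attached to this.

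**The case against.** The strongest reply is that the problem may never arise. The Background says that most Swiss practices are single-handed, and the hypothesis is set in such practices. The authors move between GP and practice as if they were the same thing. Nothing says that several GPs of one practice will enrol, and a rule of one GP per practice could stand in a full protocol that is not shown. This limits the size of the risk. It does not close the gap, because the eligibility text expressly opens the trial to group practices and the printed draw, made without knowledge of who the GPs are, cannot keep colleagues together.

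The remark about constraints should also not be over-read. It most naturally means no stratification or matching; it is not a decision to split practices.

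Full carry-over is unlikely. The GP workshops, the access to a diabetes specialist and the scheduled nurse contacts are also specific to the intervention arm, so a control GP's patients would receive only part of the package. A reader might take the 68% power as the expected result, but the article does not support that. It needs two split control GPs, complete carry-over and the loss of every cluster in the dropout allowance. At a split chance of 14/27, an average of two splits takes about four enrolled pairs (4 × 14/27 = 2.07), or 8 of the 28 GPs.

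A reader might also infer that the draw ought to be constrained on baseline HbA1c, since those data are collected before randomisation. With the plan's SD and ICC, the baseline difference between arms has a standard error of 0.157 points, and a gap of at least 0.2 has about a 20% chance. That is chance imbalance, not bias. Simple randomisation of 28 clusters is valid, and a constrained draw would require all baseline forms to be returned and entered first.

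**Conclusion.** The point holds as a gap in the allocation rule and an inconsistency about the unit. As written, the procedure can place one nurse in both arms, which would defeat the stated reason for clustering. Whether it will do so cannot be told from the article.

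The conditional part is firm: if two GPs of one practice enrol, the chance of a split is 52%. The loss of effect and power rests on assumed values for the number of affected GPs and the carry-over, and should be read as the range in the table, starting from no loss at all. The sample size is correctly calculated for independent clusters without contamination. The two descriptions of the unit need to be reconciled however many practices turn out to be shared.

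**What to change.** 1. Make the practice the unit of randomisation. Either accept one GP per practice, or allocate all participating GPs of a practice together.
2. Use the practice as the cluster in the analysis.
3. Make Study design, Sample size, Recruitment of GPs and randomization, and Intervention on the GPs name the same unit.
4. Leave the draw otherwise unrestricted. Adjust the primary comparison for the baseline HbA1c already collected; that is enough to deal with chance imbalance.

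The target of 14 clusters per arm does not change, provided that it is counted in practices. The price is that a few second GPs are declined or paired with their colleague. With pairing, a practice could bring 24 patients (2 × 12) but would still count as one cluster. The list for the draw must show which GPs share a practice; a practice code does this without revealing identities.
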